# Comparison of different weight-based scalars of remimazolam tosylate for anesthesia induction in obese patients: study protocol for a prospective, controlled trial

**DOI:** 10.1186/s13063-023-07739-6

**Published:** 2023-11-10

**Keywords:** Obese, Remimazolam tosylate, Induction dose, Lean body weight, Randomized controlled trial

## Abstract

**Background:**

The physiologic and anthropometric characteristics changes associated with obesity may result in the alternation of pharmacologic management. Remimazolam tosylate is a new type of ultra-short-acting benzodiazepine with stable context-sensitive half-time (CSHT) and no lipid accumulation after long-time infusion. Although remimazolam tosylate has potential advantages for the induction and maintenance of anesthesia in obese patients, the appropriate induction dosing scalars among obese patients are unknown. Therefore, we aim to compare the different weight-based scalars for dosing remimazolam tosylate of anesthesia induction among obese patients.

**Methods/design:**

The study will be performed as a prospective, single-center, double-blind, controlled clinical trial. The study design is a comparison of remimazolam tosylate requirements based on total body weight (TBW) or lean body weight (LBW) to reach a Modified Observer’s Assessment of Alertness and Sedation (MOAA/S) score of 0 among obese subjects (BMI ≥ 35 kg/m^2^). Another twenty normal-weight subjects (18.5 kg/m^2^ ≤ BMI < 25 kg/m^2^) will be enrolled as a control group, whose induction dose is scaled based on TBW. The infusion rate of remimazolam tosylate during induction is 12 mg/kg/h in all groups.

**Discussion:**

Results of the present study will provide evidence of dose scalar of remimazolam tosylate to guide the clinical practice of anesthesia induction in obese patients.

**Trial registration:**

Chinese Clinical Trial Registry ChiCTR220005664. Registered on 9 February 2022, https://www.chictr.org.cn/showproj.aspx?proj=151150.

## Background

Obesity is a recognized global health problem [1]. Physiological changes related to obesity alter the pharmacokinetics (PK) and pharmacodynamics (PD) and narrow the therapeutic window of anesthetics [2, 3]. Thus, it is necessary to consider the proper dose of anesthetic drugs among obese patients, particularly morbidly obese (MO) patients.

Remimazolam is a new ultra-short-acting benzodiazepines [4], which shows positive modulation on the four major subtypes (α1, α2, α3, α5) of the GABA_A_ receptor [5, 6] and is rapidly metabolized by tissue esterase to an inactive carboxylic acid metabolite [7]. The context-sensitive half-time (CSHT) of it hardly changes even after long-term infusion [8–10]. Besides, there is a specific antagonist for remimazolam in clinical settings [11]. All of the above reasons make remimazolam a potentially suitable sedation and induction anesthetic in obese patients [12, 13]. Among normal-weight patients, remimazolam is recommended to be administered according to TBW.

However, among obese patients, many factors, such as the lipophilicity of the drug, ionization properties, blood to plasma ratio, and protein binding, influence the volume of distribution (Vd) [14]. Vd is of particular significance for choosing the optimal loading dose, but TBW is not always a strongly linear increase with the Vd of a drug [14, 15]. Lean body weight (LBW) is TBW minus the weight of the fat mass, which has a higher correlation with cardiac output (CO) than the fat mass, thus making it ideal for determining loading and induction doses among obese patients [16]. In general, there is no single weight-based scalar that is undeniably better than the others for describing the PK of drugs in obese patients, who are often excluded from clinical trials, leading to a lack of evidence-based dosing recommendations for many drugs, especially new drugs [17]. Therefore, as a new drug, the dose scalar of remimazolam tosylate (based on TBW or LBW) among obese patients needs to be explored.

### Objectives

The primary trial objective is to determine an appropriate scalar (TBW or LBW) of remimazolam tosylate for anesthesia induction in obese patients by measuring the total induction dose (mg/kg) at the time of loss of consciousness (LOC).

## Methods

### Trial design and study setting

The exploratory study is designed as a prospective, double-blind controlled trial, which is conducted at the Department of Anesthesiology, Eye & ENT Hospital, Fudan University in Shanghai. It is registered in the Chinese Clinical Trial Registry (ChiCTR2200056641, Date of registration: February 9, 2022). The protocol is reported following the SPIRIT reporting guidelines [18].

### Participants

#### Eligibility criteria

Forty obese patients (18 ≤ age ≤ 65 years, American Society of Anesthesiologists (ASA) grades II to III, BMI ≥ 35 kg/m^2^) are randomized to either TBW or LBW group, while twenty normal-weight control group patients (18 ≤ age ≤ 65 years, ASA I to III, 18.5 kg/m^2^ ≤ BMI < 25 kg/m^2^) receive induction dose based on TBW (Fig. 1), who are scheduled to undergo elective eye, ear, nose, throat surgery under general anesthesia and will be enrolled in this clinical trial.

**Fig. 1 Fig1:**
[figure not shown]
Flow chart

#### Exclusion criteria

Patients who meet any of the following criteria will be excluded:Allergic reaction to any compositions of the planned medicationLong-term use of analgesics, benzodiazepines, and any prescribed or over-the-counter sleep medicationsHistory of significant cardiac, pulmonary, liver, or renal diseaseHistory of mental abnormalitiesLong-term drinking historyParticipated in clinical trials of drugs as subjects in recent 3 monthsHistory of difficult tracheal intubation, or an anticipated difficult airway scheduled for awake fiberoptic intubation

The schedule of enrollment, intervention, and assessment is reported according to the SPIRIT statement (Fig. 2).

**Fig. 2 Fig2:**
[figure not shown]
SPIRIT timeline of this trial

The number of excluded patients and the reasons for their exclusion will be reported according to the SPIRIT statement.

#### Consent

At least 1 day before the day of surgery, the researchers will screen the potential participants from the list of scheduled operations according to the inclusion and exclusion criteria. Patients who meet the inclusion/exclusion criteria will be given written informed consent and preoperative evaluation.

The principal investigator or physician who examines the subject may decide to remove the subject from the study if the subject has an emergency medical problem (allergic reaction or acute health problem).

### Ethical approval

The study protocol (V1.0, issue date January 2022) has been approved by the Ethics Committee of Eye & ENT Hospital, Fudan University in Shanghai (2022012).

### Assignment of interventions: randomization and allocation

Forty obese patients are randomly allocated in a 1:1 ratio to either the TBW group or the LBW group after they sign the informed consent form. An independent statistician who was not directly involved with the study randomly allocated the obese patients into the TBW or LBW group according to a computer-generated randomization scheme. Patient assignments will be placed in sequentially numbered, opaque, sealed envelopes. The randomization scheme is kept inaccessible throughout the study period.

After the obese subject enters the operation room, the research nurse, who does not participate in anesthesia, will open the sealed envelope for random numbers, calculate, and set the infusion speed according to the group information.

### Assignment of interventions: blinding and procedure for unblinding if needed

Considering that the attending anesthesiologist and anesthesia assistant will be responsible for observing the clinical manifestations, including scoring of MOAA/S, they should be blinded to the allocation of the obese groups. The subjects of obese groups are blinded to the allocation. In the events of serious adverse events (SAEs) such as a medical emergency, which require identifying the intervention administered to the patient, the attending anesthesiologist or anesthesia assistant is permitted to inquire with the unblinded research nurse. Due to the induction dose based on TBW in the control group, it is difficult to double-blind.

### Intervention

#### Preparation before general anesthesia

Benzodiazepines as premedication in the study are not allowed to be provided. Other kinds of anti-anxious drugs, such as clonidine, are allowed to be provided on the night before surgery. After routinely fasting before the operation, we will insert an 18- or 20-gauge peripheral IV catheter into the subject’s left or right forearm and continuously infuse normal saline of 5 ml/kg prior to the induction of general anesthesia. All obese subjects are positioned in the “ramped” position (elevate the patients’ upper body and head) to achieve horizontal alignment between the external auditory meatus and sternal notch [19]. Heart rate (HR), noninvasive blood pressure (BP), electrocardiogram (ECG), end-tidal carbon dioxide (ETCO_2_), and pulse oxygen saturation (SpO_2_) are routinely monitored (Mindray BeneView T8, Shenzhen Mindray Bio-Medical Electronics Co) during the induction and maintenance of general anesthesia. BIS sensor (BIS™XP, Medtronic) will be applied to monitor the depth of anesthesia and the BIS value will be recorded. The acceleromyography (TOF-watch SX; MSD) will be used to monitor muscle relaxation. Keep the operation room quiet, and the patients are asked to keep their eyes closed during induction.

#### Induction of general anesthesia

After routine monitoring, preoxygenation will be given with a mask by using 100% oxygen at a flow rate 8 L/min; the anesthesia assistant will ask the patients to deep breathe continuously. The administration of the study drug will begin when the end-tidal concentration of oxygen is stable above 90% [20]. The administration time is defined as the beginning of anesthetic induction (t_0_).

For obese subjects, the remimazolam tosylate (36 mg, prepared as a 2 mg/ml solution with normal saline) will be infused at the infusion rate of 12 mg/kg/h based on TBW (*n* = 20) or LBW (*n* = 20). LBW is calculated using the Janmahasatian equation [21].$$\begin{array}{l}\mathrm{LBW\, }(\mathrm{kg})\mathrm{\, in\, men }= \frac{9270\cdot TBW}{6680+(216\cdot BMI)}\\ \mathrm{LBW\, }(\mathrm{kg})\mathrm{ \,in\, women }= \frac{(9270\cdot TBW)}{8780+(244\cdot BMI)}\end{array}$$

For normal-weight control group (*n* = 20), remimazolam tosylate (2 mg/ml) will be infused at the infusion rate of 12 mg/kg/h based on TBW. Thirty seconds after administration, the investigator will assess the change in the level of consciousness every 10 s using the responsiveness scores of the Modified Observer’s Assessment of Alertness/Sedation Scale (MOAA/S) (Table 1) [22]. When the subject gives a negative response on opening his or her eyes and moving his or her toes, then he or she will be given a painful trapezius squeeze. Loss of consciousness (LOC) is confirmed when the first MOAA/S score reaches zero (i.e., the patient does not respond to a painful trapezius squeeze). The investigator will record the time required for LOC, and the value of BIS, HR, and BP. At MOAA/S of zero, the induction dose will be stopped, and the maintenance dose of remimazolam tosylate from 1 mg/kg/h (calculated by TBW, up to 3 mg/kg/h) will be continued. After LOC, all MO subjects are given rocuronium (0.6 mg/kg, IV. IBW) and sufentanil (0.2 μg/kg, IV. LBW). Visible arm movement during rocuronium administration is defined as rocuronium injection pain. IBW is calculated using the following formula.

**Table 1 Tab1:** Modified Observer’s Assessment of Alertness/Sedation

Responsiveness	Score
Responds rapidly to name spoken in normal tone	5 (alert)
Lethargic response to name spoken in normal tone	4
Responds only after name is called loudly and/or repeatedly	3
Responds only after mild prodding or shaking	2
Responds only after painful trapezius squeeze	1
Does not respond to painful trapezius squeeze	0

$$\begin{array}{l}\mathrm{IBW\, in\, men }=\mathrm{ height }\left(\mathrm{cm}\right)-105\\ \mathrm{IBW\, in\, women }=\mathrm{ height }\left(\mathrm{cm}\right)-110\end{array}$$

All patients will be mask-ventilated after LOC, and the SpO_2_ during induction (from the administration of remimazolam tosylate to 5 min after securing the airway) will be recorded. If necessary, the oropharyngeal airway will be used for the maintenance of oxygenation. When the train-of-four (TOF) value is 0, the endotracheal intubation or supraglottic airway devices (SADs) will be placed. Then, pressure-controlled ventilation with a breathing frequency of 10–12 times/min, a ratio of inspiratory to expiratory of 1:1.5–2, and a tidal volume of 8–10 mL/kg (IBW) will be performed. The respiratory parameters will be adjusted to maintain the ETCO_2_ between 35 and 45 mmHg.

#### Maintenance of general anesthesia

After LOC, the infusion rate in both groups will be adapted for maintaining the depth of anesthesia starting at a dose of 1 mg/kg/h (calculated by TBW, upper limit: 3 mg/kg/h) based on clinical signs and symptoms, such as changes in BP, HR, and keep BIS value between 40 and 60. If EMG or electrical signal interference is eliminated, the BIS value is above 60 for more than 3 min, the infusion rate of remimazolam tosylate will be increased by 0.2 mg/kg/h each time. The dose of anesthetic drugs during general anesthesia, such as remifentanil and rocuronium, will be recorded.

#### Recovery from general anesthesia

All patients will be transferred to the post-anesthesia care unit (PACU) after the surgery; they will be positioned head-up. The sugammadex (2 mg/kg, IV TBW) and flumazenil (0.5 mg per patient) are given and the patients will be sent back to the ward according to the clinical protocol and the PACU physicians’ judgments.

### Outcomes

#### Definition of the primary outcome

The primary outcome of the study is the calculated dose of per kilogram remimazolam tosylate requirement from the time point of remimazolam tosylate starting infusion to the time point of the MOAA/S score reaching zero (LOC).

#### Assessment of primary outcome

The dose requirement of remimazolam tosylate during the induction period will be calculated according to the dose per kilogram TBW in the TBW group or LBM in the LBW group. The dose requirement of remimazolam tosylate of the control group during the induction period will be calculated based on TBW.

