#### Definition of secondary outcomes

The secondary outcomes include the time from the start of remimazolam infusion to MOAA/S zero, total induction dose of remimazolam tosylate when MOAA/S reaches zero, the BIS value and hemodynamic variables (HR, BP) at the baseline, MOAA/S zero and 1 min after intubation, adverse events during induction (such as injection pain, hiccup, bucking…), the dose of remifentanil, the BIS value during maintenance, and the total time stay in PACU.

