### Statistical analysis

#### Statistical analysis for primary and secondary outcomes

Baseline clinical and demographic characteristics will be summarized and reported using descriptive statistics. Categorical variables will be reported as numbers and percentages and will be compared using the chi-square test or Fisher’s exact test, as appropriate. The Shapiro-Wilks test will be used to first verify the normality of the continuous variables and will be reported as means and standard deviations or as medians and interquartile ranges. Continuous variables will be compared using Student’s *t* test or the Mann-Whitney *U* test, as appropriate.

The primary analysis will examine the difference in primary outcome between groups and will be reported as an absolute difference; an unpaired two-tailed t test will be used to test the statistical significance of the mean difference between the three groups. Then, the primary outcome will be analyzed using a linear mixed model adjusted by a set of baseline variables (gender or age) that are strongly believed to affect the outcome. Secondary outcomes will be analyzed using linear, logistic, or ordered regression analysis methods as appropriate, with the same adjustments as the primary outcomes. The primary analysis will be conducted according to the intention-to-treat principle, and per-protocol analysis will be performed and reported separately. All estimated treatment effects will be accompanied by 95% confidence intervals and p-values. Analysis will be performed by use of SPSS statistical package (IBM, version 21.0; SPSS).

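### The primary outcome is time to loss of consciousness in other units, and the randomised TBW-versus-LBW difference in it is expected to have the same sign whichever scalar is right

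*Protocol article*

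**What the plan says.** Under Objectives, the article sets out to choose between TBW and LBW from the mg/kg dose at LOC. Four statements then fix how that works.

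- **Rate.** The abstract's Methods/design says "The infusion rate of remimazolam tosylate during induction is 12 mg/kg/h in all groups". Induction of general anesthesia makes clear that the kilogram is TBW in one obese arm, LBW in the other, and TBW in controls.
- **Stopping point.** "At MOAA/S of zero, the induction dose will be stopped".
- **Denominator.** Under Assessment of primary outcome, the dose in the obese arms "will be calculated according to the dose per kilogram TBW in the TBW group or LBM in the LBW group" (LBM evidently means LBW), and the requirement "of the control group during the induction period will be calculated based on TBW".
- **Analysis.** "The primary analysis will examine the difference in primary outcome between groups and will be reported as an absolute difference", with an unpaired two-tailed t test across the three groups. Only the two obese arms are randomised against each other.

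The secondary outcomes include "the time from the start of remimazolam infusion to MOAA/S zero, total induction dose of remimazolam tosylate when MOAA/S reaches zero". No stated rule says which result would favour which scalar.

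**The concern.** The scalar that sets the pump also divides the dose. Subtracting mg per kg TBW from mg per kg LBW is not a difference in drug requirement; it is a difference in elapsed time. The LBW arm gets fewer mg per hour at the same body size, so it should take longer to reach LOC under either hypothesis. A comparison that points the same way under both hypotheses cannot decide between them, yet it is the trial's only randomised comparison.

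Two misreadings follow. A significant TBW–LBW difference could be taken as evidence about the right scalar. A matching difference in time to LOC could be taken as support, although it is the same variable.

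**Working it through.** **Plan's own figure.** With difference 0.1, SD 0.08, two-sided alpha 0.025 and power 90%: n = 2 × (2.241 + 1.282)² × 0.08² / 0.1² = 15.9, so 16. Then 16/0.8 = 20 per group. The stated sample size reproduces and is not in dispute.

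**Identity.** 12 mg/kg/h ÷ 3600 = 1/300 mg/kg per second. Dose ÷ own scalar = seconds/300 in every arm. The 0.1 mg/kg design difference is therefore 30 s.

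**Inputs.** Let f = LBW/TBW from the article's equations: 9270/(6680 + 216·BMI) for men and 9270/(8780 + 244·BMI) for women. At BMI 40, f = 0.605 (men) and 0.500 (women). At BMI 22, assumed for controls, fc = 0.811 and 0.655. The Discussion cites 88.7 s at 12 mg/kg/h and 102 s at 6 mg/kg/h, so the reference reading is 88.7/300 = 0.296 mg/kg TBW. That study used unresponsiveness to shoulder shaking, not MOAA/S 0, as its endpoint.

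**Model A: total mg at LOC does not depend on infusion rate.**
- TBW right: TBW arm 0.296; LBW arm 0.296/f.
- LBW right: TBW arm 0.296·f/fc; LBW arm 0.296/fc.
- The LBW:TBW ratio is 1/f under both.

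**Model B: time to LOC rises as the rate falls, as in the cited times.** Time ∝ rate^(−g), with g = log₂(102/88.7) = 0.202.
- TBW right: TBW arm 0.296; LBW arm 0.296·f^(−g).
- LBW right: TBW arm 0.296·(fc/f)^(−g); LBW arm 0.296·fc^(−g).
- The LBW:TBW ratio is f^(−g) under both.

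Own-scalar readings at BMI 40 (mg/kg):

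| Model, sex | TBW right: TBW arm / LBW arm | Excess | LBW right: TBW arm / LBW arm | Excess |
|---|---|---|---|---|
| A, men | 0.296 / 0.489 | +0.19 | 0.221 / 0.365 | +0.14 |
| A, women | 0.296 / 0.591 | +0.30 | 0.226 / 0.451 | +0.23 |
| B, men | 0.296 / 0.327 | +0.03 | 0.279 / 0.308 | +0.03 |
| B, women | 0.296 / 0.340 | +0.04 | 0.280 / 0.322 | +0.04 |

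Over BMI 35 to 45, the excess under A is 0.16 to 0.33 if TBW is right and 0.13 to 0.24 if LBW is right. With 16 completers per arm, SD 0.08 and alpha 0.025, power is about 0.99 or more. Under B the excess is 0.027 to 0.049 if TBW is right and 0.026 to 0.046 if LBW is right (8 to 15 s), with power about 0.09 to 0.30. The ASA III times in the Discussion (97.2 s and 81.7 s) give 0.03 to 0.06.

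**Would a common scale rescue the randomised contrast?** Under A, total mg is equal in the two arms whichever scalar is right. Under B, the LBW:TBW ratio of total mg is f^(1−g). At BMI 38 (f = 0.623 and 0.514) that is 0.69 for men and 0.59 for women, under either truth. On mg/kg TBW the LBW arm then reads about 0.09 to 0.12 lower under either truth. So no.

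**Contrasts with control (BMI 40).**
- TBW-obese minus control, mg/kg TBW: 0 if TBW is right. If LBW is right, about −0.07 (A) or 0.280 − 0.296 ≈ −0.02 (B).
- LBW-obese minus control as now defined (LBW against TBW): +0.07 (men) to +0.16 (women) under A even if LBW is exactly right.
- LBW-obese minus control, mg/kg LBW in both: under A, 0 if LBW is right and +0.12 to +0.14 if TBW is right. Under B, control reads 0.296/fc = 0.365 or 0.451, so the difference is −0.06 (men) and −0.13 (women) if LBW is right, and −0.04 and −0.11 if TBW is right. Controls still receive more mg per kg LBW per hour.

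**The case against.** The strongest reply is that the trial is not limited to the randomised contrast. The analysis section names three groups, and TBW-obese versus control shares both scalar and rate per kilogram, so it discriminates. The study calls itself exploratory, total mg is already collected, and a propofol study cited in the Discussion used time to LOC to favour LBW, so equivalence to time does not by itself make the outcome useless. All of this stands. It limits the point to the direct TBW–LBW test and to the absence of any statement of which contrast decides. It does not rescue that test. Nor can the gap be left to an analysis plan, because the article itself fixes the denominators.

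Three stronger readings are tempting, and the documents do not support them.

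- *The artefact is sure to be significant and larger than 0.1 mg/kg.* That needs total mg at LOC to be independent of rate. The article's own times give 6 × 102/3600 = 0.170 mg/kg at the slower rate against 0.296 at the faster, so dose does depend on rate.
- *The trial cannot inform the choice at all.* The TBW-obese versus control contrast can.
- *Moving the randomised comparison to total mg or mg/kg TBW cures it.* Under the same rate dependence the sign is again fixed, now in the opposite direction.

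**Conclusion.** The point holds for the randomised TBW-versus-LBW test. That the outcome equals seconds/300 is exact, given a constant infusion stopped at LOC. The direction is an expectation, resting only on a slower infusion taking longer, which both pairs of times cited in the Discussion show. Under both models the expected ratio of the two arms is identical whichever scalar is right, so this contrast cannot select one.

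The size is uncertain: about 0.03 to 0.05 mg/kg with the cited rate dependence, and about 0.1 to 0.3 mg/kg without any. Assumptions not in the documents are obese BMI 35 to 45, control BMI 22, and the power-law extrapolation from a different LOC endpoint.

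The contrast that does inform the choice may be small. The standard error with 16 per group is 0.08 × √(2/16) = 0.028 mg/kg, against an expected −0.07 (power about 0.6) or −0.02 (power about 0.05) if LBW is right.

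**What to change.** Amend Assessment of primary outcome and the statistical analysis section as follows.

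1. State that the direct TBW–LBW difference, on own-scalar mg/kg or on total mg, is descriptive and does not select the scalar.
2. Base the choice on named contrasts of the obese arms with the normal-weight control, with one denominator in both groups: mg/kg TBW for TBW-obese versus control, and mg/kg LBW for LBW-obese versus control. Say which result would favour which scalar.
3. Note that in the LBW contrast the infusion rate per kg LBW still differs between the groups, so a non-zero difference there is not by itself evidence against LBW.
4. Report total mg, mg/kg TBW and mg/kg LBW for all three groups.
5. State that own-scalar mg/kg and time to LOC are one variable, and count them once.

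Cost: an amendment to the primary-analysis wording while recruitment is under way, before the data are analysed. No new data are needed, since TBW, LBW and total induction dose are already recorded. The downside is that the deciding contrasts are not randomised, and the control group is not blinded in the way the obese arms are, so conclusions about the scalar need to be worded accordingly.

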### Data collection

Before surgery, general information (age, gender, height, TBW, BMI, LBW, IBW, ASA status, Mallampati score) and the surgical methods of the patients are investigated, and indexes such as albumin, alanine aminotransferase (ALT), and aspartate aminotransferase (AST) are recorded. Baseline BIS, HR, SBP, DBP, and MAP are recorded before induction (-t_1_). During induction, BIS and the hemodynamic profiles are recorded at the following time points: MOAA/S 0 (t_1_), before airway security (t_2_), 1 min after airway security (t_3_), beginning of operation (t_4_), the end of operation (t_5_), discharging from PACU (t_6_). The minimum SpO_2_ during induction (from administration to 5 min after intubation) will be recorded. Time from the start of administration of the remimazolam tosylate to MOAA/S 0, time from the end of administration to extubation, and time from the end of administration to discharge from the PACU are also recorded.

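### The control dose is expressed per kg TBW only, so matching control is not what a correct lean-weight scalar predicts for the LBW arm

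*Protocol article*

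**What the plan says.** The Objectives section sets out to "determine an appropriate scalar (TBW or LBW) of remimazolam tosylate for anesthesia induction in obese patients", using the mg/kg dose at loss of consciousness (LOC). Under Assessment of primary outcome, the obese arms are expressed "according to the dose per kilogram TBW in the TBW group or LBM in the LBW group" (LBM evidently means LBW). For the reference group: "The dose requirement of remimazolam tosylate of the control group during the induction period will be calculated based on TBW".

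The primary analysis then states that "an unpaired two-tailed t test will be used to test the statistical significance of the mean difference between the three groups". The abstract adds: "The infusion rate of remimazolam tosylate during induction is 12 mg/kg/h in all groups". Each group's rate refers to its own scalar.

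The baseline data include "general information (age, gender, height, TBW, BMI, LBW, IBW, ASA status, Mallampati score", and total induction dose is a secondary outcome. No section plans a control dose per kg LBW. No section states how the test results lead to a choice of scalar.

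**The concern.** The TBW arm and the control group share a unit. The LBW arm and the control group do not. Normal-weight people also weigh more than their lean mass, so a requirement that follows lean weight perfectly gives the same mg per kg LBW in both groups, but not the same number when one group is divided by LBW and the other by TBW.

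The control group has no evident purpose in the primary comparison except as the benchmark for the two obese arms. If a reader takes nearness to control as the sign of the right scalar, part of what is read is the unit difference. The answer to the primary question is at stake.

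**Working it through.** **The plan's own figure.** With a difference of 0.1, SD 0.08, two-sided alpha 0.025 and 90% power: 2 × (2.241 + 1.282)² × (0.08/0.1)² = 15.9, so 16 per group; 16/0.8 = 20. The stated 20 is reproduced, so 0.1 mg/kg is the yardstick.

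**Inputs from the protocol.** The LBW equation (Induction of general anesthesia); control BMI 18.5 to below 25 and obese BMI 35 or more (Eligibility criteria); times to LOC of 102 s at 6 mg/kg/h and 88.7 s at 12 mg/kg/h (Discussion).

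**Assumptions.** Typical BMI 22 (control) and 40 (obese), half men, and a control dose of 12/3600 × 88.7 = 0.296 mg/kg TBW. The cited times use a shoulder-shaking endpoint, not MOAA/S 0. In all that follows, lean weight is taken to be exactly the right scalar.

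**Step 1: LBW/TBW.**
- BMI 22: men 9270/(6680 + 216×22) = 0.811; women 9270/(8780 + 244×22) = 0.655; half men 0.733.
- BMI 40: men 0.605; women 0.500; half men 0.553.
- Over the control BMI range: 0.62 (women, 24.9) to 0.87 (men, 18.5), always below 1.

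**Step 2: infusion rate per kg LBW.** Controls receive 12/0.811 = 14.8 (men) or 12/0.655 = 18.3 (women) mg/kg LBW/h. The LBW arm receives 12.

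**Step 3: constant mg per kg LBW.** LBW arm minus control = 0.296/ratio(control) − 0.296. TBW arm minus control = 0.296 × ratio(obese)/ratio(control) − 0.296.

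| BMI 22 / 40 | LBW − control | TBW − control |
|---|---|---|
| Men | +0.069 | −0.075 |
| Women | +0.156 | −0.070 |
| Half men | +0.108 | −0.073 |

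Averaging the two sex-specific LBW gaps instead gives +0.112. Over the control BMI range the LBW gap runs from +0.045 (men, 18.5) to +0.178 (women, 24.9). A gap of 0.108 with SD 0.08 and alpha 0.025 is significant with probability 0.92 (n = 16) to 0.97 (n = 20).

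**Step 4: dose that depends on rate.** The cited times give 6/3600 × 102 = 0.170 and 0.296 mg/kg, a difference of 0.126, in line with the 0.12 in the sample size section. If time to LOC falls as a power of the rate per kg LBW, the exponent is ln(102/88.7)/ln 2 = 0.20. With half men and BMI 22/40:
- LBW arm: 88.7 × (12/16.4)^−0.20 = 94.4 s, which is 0.315 mg/kg, a gap of +0.019.
- TBW arm: rate 12/0.553 = 21.7; 83.8 s; 0.279 mg/kg; a gap of −0.016.

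The LBW gap runs from about +0.009 to +0.029 over control BMI and sex. A gap of 0.02 is significant with probability 0.06 to 0.07.

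**Step 5: the same contrast per kg LBW.** Control becomes 0.296/0.733 = 0.403 mg/kg LBW. Under Step 3 the LBW arm is also 0.403, so the gap is 0. Under Step 4 it is 0.315 − 0.403 = about −0.09 (range −0.04 to −0.15), because controls were infused faster per kg LBW.

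**The case against.** The strongest reply is that the units are deliberate. Every group runs at 12 mg/kg/h of its own scalar, so the primary outcome is the same multiple of time to LOC everywhere. The comparison then asks whether the standard mg/kg figure, applied to TBW or LBW in obese patients, behaves as it does in normal-weight patients, for whom the Background gives TBW as the recommended basis. That is a fair practical question, and the existing contrast should stay for it. The protocol does not say that this is the question, however; its objective is to find the appropriate scalar.

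A reader might go further and infer that the comparison will reject LBW and make TBW look closer even when LBW is right. The documents do not support that:
- The high rejection probability needs a dose at LOC that does not depend on infusion rate. The protocol's own times say that it does, and the gap then falls from about +0.11 to about +0.02.
- Even with a constant dose, LBW is the closer arm for men at BMI 22/40 (0.069 against 0.075), and for half men with control BMI 18.5 and obese BMI 40 (0.082 against 0.087).
- No section says that the scalar nearer to control is chosen, and the study is described as exploratory.

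It is also fair to object that moving the control group to per kg LBW is no neutral cure. Step 5 shows that this can create a false gap of about −0.09. That stands, and it shapes the fix.

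**Conclusion.** The point holds in a limited form. The unit choice is stated, not left open, and it means that equality with control is not the prediction of a correct lean-weight scalar. The resulting offset is always upward. It is about 0.05 to 0.18 mg/kg with a constant requirement per kg LBW, which is of the order of the design difference, and about 0.01 to 0.03 with the rate dependence implied by the cited times. Sex mix, mean BMI and control dose are assumptions, and the rate relation rests on two mean times at a different endpoint. The direction of any wrong choice cannot be foretold. Nearness to control in mixed units is simply not enough to identify the scalar. The correction is worth making before analysis because it needs no new data.

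**What to change.** - Derive dose at LOC per kg TBW and per kg LBW for all 60 patients from the recorded total mg, TBW and LBW.
- Keep the existing LBW-arm contrast, labelled as the practical question of whether the standard mg/kg figure carries over to LBW.
- Beside it, report the LBW arm against control per kg LBW and the TBW arm against control per kg TBW.
- Report each group's infusion rate per kg LBW. The per-kg-LBW contrast should neither replace the primary one nor be read alone.
- Base the choice of scalar on an analysis of all patients that accounts for the rate, for example time or total dose at LOC modelled on rate per kg LBW versus rate per kg TBW. The design separates the two. At BMI 40 the TBW arm runs at 12/0.605 = 19.8 (men) or 12/0.500 = 24.0 (women) mg/kg LBW/h, against 12 in the LBW arm.

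No patient is treated differently and nothing more is collected. The cost is a little more analysis, and a conclusion on the scalar that may be less clear-cut.
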